#### Biomarkers

Differences of each biomarker (complete bold count, C reactive protein, plasma albumin and fecal calprotectin will be analyzed intra-individually between T0 and T3 to ascertain the evolution trend for each subject. Then, participants will be divided into three different subpopulations: low-profile (those who are below the reference interval for a given analyte), median-profile (those who fall within the reference interval) and high-profile (those who are above the reference interval). The percentage of individuals who change from the initial (at T0) to another profile at the end of 12 months (T3) will be determined.

Gut microbiota was also analyzed at T0 and T3. Faces were collected at both time points, and total DNA was extracted. The V3–V4 region of 16S rDNA gene was amplified by Polymerase Chain Reaction (PCR), and the amplicons will be pooled at equimolar concentrations and sequenced using high throughput techniques. GelComparII (Applied Maths, Sint-Martens-Latem, Belgium) will be used to analyze and compare bacteria profiles. Cluster analysis will be performed using the UPGMA method (group average method), applying Pearson correlation coefficient. Diversity (Shannon–H') index of bacterial communities will be calculated using PAleontological STatistics (PAST) version 1.34. Significance of differences among diversity index will be performed using the *t*-test through PAST.

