### Aims of this Study

This study aims to conduct a two-arm RCT to test the efficacy of a new integrative ACT and compassion-based intervention, the Living with Intention, Fullness, and Engagement with Inflammatory Bowel Disease (LIFEwithIBD) intervention, which was adapted from the Mind programme for people with cancer (52) to the IBD context. This intervention (LIFEwithIBD + TAU)'s superiority in improving psychological distress (primary outcome), quality of life, work and social functioning, IBD symptom perception, illness-related shame, psychological flexibility, self-compassion, disease activity, inflammation biomarkers, and gut microbiota diversity will be compared to TAU.

The contents of the LIFEwithIBD intervention and the design of the RCT are presented in this paper.

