##### Biomarkers

An erythrogram, leukogram, and thrombogram were obtained from all participants since hematological alterations such as anemia, thrombocytosis and leukocytosis, may be observed in some patients, in particular during flares. C Reactive Protein (CRP) was also determined (by immunoturbidimetry) since it is an acute-phase reactant and therefore is a reliable biomarker to assess inflammatory states. Hence, although not specific for IBD, CRP is regularly monitored in patients in order to assess the degree of intestinal inflammation. Finally, serum albumin was determined (by colorimetry) since it tends to decrease rather quickly in severely ill patients. In fact, hypoalbuminemia is frequently observed in patients with uncontrolled disease or with prolonged and frequent flares (84). The blood specimens were analyzed according to the Coulter principle (impedance).

In order to assess a specific biomarker, intestinal inflammation was investigated by quantifying fecal calprotectin. Indeed, fecal calprotectin is a valuable and sensible tool to monitor IBD progression and anticipate relapses, correlating well with the degree of endoscopic and histological inflammation (85). Fecal calprotectin was determined using Buhlmann's Quantum Blue® fcal assay. Briefly, calprotectin was extracted from stools using a Calex® cap pre-filled with extraction buffer and applied to a lateral flow test cassette adsorbed with a monoclonal antibody against human calprotectin. The cassette was then inserted into Buhlmann Quantum Blue® reader which immediately started the reading process, converting the image analysis into a quantitative result (μg/g).

Gut microbiome was sequenced in the stools of patients before and after the psychological intervention in an attempt to establish a mechanist link between bacteria richness and diversity with disease progression (in terms of clinical and psychological outcomes) and biochemical indicators.

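### Superiority over TAU is claimed for inflammation biomarkers and gut diversity, but no between-arm analysis is fixed for the biomarkers and the contrast for diversity is unnamed

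*Protocol article*

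**What the plan says.** The protocol's Aims of this Study sets up a superiority comparison over a list of outcomes that ends with "inflammation biomarkers, and gut microbiota diversity will be compared to TAU". Table 2 places C-reactive protein, hemogram, albumin, fecal calprotectin and gut microbiota among the secondary outcomes, sampled at t0 and t3.

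Their analysis stands in the Biomarkers subsection of Data Analysis:

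- Each blood or fecal marker "will be analyzed intra-individually between T0 and T3 to ascertain the evolution trend for each subject".
- Next comes a sorting of people into three classes for every marker. The first class is "low-profile (those who are below the reference interval for a given analyte"; the remaining two lie inside and over that range.
- The summary built on these classes reads: "The percentage of individuals who change from the initial (at T0) to another profile at the end of 12 months (T3) will be determined".
- For microbiota there is a cluster analysis and a Shannon index, with a t-test to follow: "Significance of differences among diversity index will be performed using the" named test. What is compared with what is not stated.

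The Biomarkers text under the outcome measures describes sequencing before and after the intervention "in an attempt to establish a mechanist link between bacteria richness and diversity with disease progression". It mentions no arm contrast.

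**The concern.** The stated aim and the stated analysis do not meet. The aim is a comparison of randomised arms. The biomarker analysis is a within-person description followed by a percentage that carries neither arm nor direction.

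The protocol's Introduction describes IBD as alternating unpredictably between active disease and remission. Over 12 months, marker changes within one group mix natural course and regression to the mean with any effect of the intervention. Randomisation separates these, but only if the arms are contrasted. Without such a contrast, no statement that the intervention improved inflammation relative to TAU could rest on this analysis. For diversity, the choice between an arm comparison and a before-after comparison would be left open until the data are in hand.

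**Working it through.** **1. Is there a planned figure to reproduce?** None is given for these outcomes. The only sample-size figure, a total of 58, is for the primary analysis. It reproduces: SMD 0.75, alpha 0.05 (two-sided assumed), 80% power and 1:1 allocation in a two-sample t-test give 28.9, so 29 per arm and 58 in total. It implies nothing about power for biomarkers.

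**2. Which planned analyses contrast the arms, and do they cover these outcomes?**

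| Protocol section | Contrast | Biomarkers or microbiota listed? |
|---|---|---|
| Data Analysis (primary) | Between arms, ANCOVA, 8 weeks | No (DASS-21 only) |
| Secondary Analyses | Between arms, ANCOVA, 8 weeks | No |
| Longitudinal Outcomes | Group by time, MMRM | No |
| Exploratory Outcomes | McNemar, within group | Not named; no arm contrast in any case |
| Biomarkers: blood and fecal markers | Within person, T0 to T3 | Yes; no arm named |
| Biomarkers: Shannon index | t-test, groups unnamed | Yes; contrast unknown |

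The ANCOVA and MMRM sections itemise their outcomes. The 8-week ANCOVA could not have covered the samples anyway, because they were taken only at T0 and T3.

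**3. Would tabulating the profile percentage by arm be enough?** Let *i* be the proportion moving towards the reference interval and *w* the proportion moving away. The stated summary is *i* + *w*; the quantity of interest is closer to *i* − *w*. The rates below are assumed, since the protocol gives none.

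| Example | Arm A (*i*, *w*) | Arm B (*i*, *w*) | Changed, A and B | Net, A and B | Net difference |
|---|---|---|---|---|---|
| 1 | 20%, 0% | 0%, 20% | 20%, 20% | +20, −20 | 40 points |
| 2 | 30%, 10% | 10%, 30% | 40%, 40% | +20, −20 | 40 points |

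In both examples the stated summary differs by 0 while the arms move in opposite directions. Splitting by arm without direction is therefore not enough.

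**4. What could a directed comparison detect at this trial's size?** Using Example 2, two-sided alpha 0.05:

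- Percentage improved, 30% v 10%: power = Φ{[0.2√n − 1.96√(2 × 0.2 × 0.8)] / √(0.21 + 0.09)}. At n = 29 per arm this is about 48%; at an assumed 20 per arm after attrition, about 35%.
- Net shift scored +1, 0, −1: SD = √(0.40 − 0.04) = 0.6, difference 0.4; power = Φ[0.4 / (0.6√(2/n)) − 1.96]. At 29 per arm this is about 72%; at 20 per arm, about 56%.

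Even a large assumed effect is not reliably detected through classes, which favours analysing the measured values.

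**5. Shannon index.** If the t-test compares arms at T3 without adjustment, its standard error relative to ANCOVA on baseline is 1/√(1 − r²). With r assumed, this is 1/√0.75 = 1.15 at r = 0.5 and 1/√0.51 = 1.40 at r = 0.7. If it compares time points, it does not address the superiority aim.

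**The case against.** The strongest reply is that silence is not a decision. The aims name the comparison with TAU, all analyses are declared intent-to-treat, and Table 2 does not restrict these samples to one arm, although it does so for the acceptability questions. A condensed article may leave table layout, pairing and direction to a fuller plan. This stands as a reason to expect that the arms could be tabulated. It does not remove the mismatch: the same article names the contrast, time point and covariate for its other secondary outcomes, while for the biomarkers it specifies a different procedure.

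Several stronger readings are tempting but not supported:

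- *The arms are never compared on gut diversity.* A reader might infer this, but a t-test is planned with its groups unnamed. An arm contrast is neither stated nor excluded, so the fault is an unspecified contrast.
- *Improvement and worsening are counted alike throughout.* This applies only to the profile percentage. The within-person differences keep their sign, and the Shannon index is continuous. A table by starting and ending profile would also fit the wording, though the text does not ask for one.
- *The low class is invalid.* The scheme is generic across analytes, and the protocol itself treats low albumin and anemia as informative. For CRP and calprotectin the class is at most uninformative.
- *Large precision losses.* A factor of 1/√(1 − r), or 1.41 to 1.83 at r = 0.5 to 0.7, applies to ignoring pairing in a within-group T0 to T3 contrast, not to the between-arm comparison. An efficiency of about 64% belongs to a split at the median, not to three reference-interval classes.

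It is also fair that these are secondary outcomes for which no power is claimed.

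**Conclusion.** The point holds in limited form. For blood count, CRP, albumin and fecal calprotectin, the stated superiority aim has no matching between-arm analysis, and the one summary measure can be identical in two arms that move in opposite directions. For Shannon H', the comparison is unspecified and no baseline adjustment is stated.

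The mismatch follows from the text alone. The sizes are illustrations: the 40% v 40% example rests on assumed transition rates, and the 1.15 to 1.40 factor on assumed baseline correlations and on the t-test being an unadjusted arm comparison at T3. The primary DASS-21 analysis and its sample size are untouched, so this should be corrected before the biomarker data are analysed but does not threaten the trial's main conclusion.

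**What to change.** 1. For each blood and fecal marker, estimate the between-arm difference at T3 by ANCOVA with the T0 value as covariate and a 95% confidence interval. Use the log scale for skewed markers such as CRP and calprotectin, so that the result is a ratio.
2. Keep the reference-interval profiles as a descriptive table only, by arm and by direction (towards or away from the interval).
3. Compute Shannon H' per participant and analyse the T3 value with the same baseline-adjusted between-arm model, in place of the t-test with unnamed groups.
4. Label these analyses secondary or exploratory, given the number of analytes and the likely loss of participants by T3; the protocol's Discussion calls retention the greatest limitation.

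If the investigators do not want a between-arm analysis, the alternative is to withdraw the superiority aim for these outcomes and call them descriptive.

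The samples are already scheduled at T0 and T3, so the cost is wording and analysis work. The small downside is more tests without multiplicity control, which is why the results should be read as estimates with intervals. ANCOVA is one sound choice; the essential change is a named, baseline-adjusted contrast between arms.

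### The t-test on Shannon diversity has no stated contrast, pairing or unit; a patient-level ANCOVA between arms, adjusted for baseline, would answer the stated aim and be at least as precise

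*Protocol article*

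**What the plan says.** All of this is in the protocol article.

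- **Sampling.** Data Analysis, Biomarkers: "Gut microbiota was also analyzed at T0 and T3", that is, at baseline and at 12 months, so each patient can contribute two stool samples.
- **Data.** The material is 16S amplicons, and "the amplicons will be pooled at equimolar concentrations and sequenced using high throughput techniques".
- **Clustering.** "Cluster analysis will be performed using the UPGMA method (group average method), applying Pearson correlation coefficient".
- **Index and test.** Shannon H' is the only index named. The inference on it is one sentence: "Significance of differences among diversity index will be performed using the *t*-test through PAST".
- **Target.** The other Biomarkers subsection, under Primary and Secondary Outcomes in the RCT, gives the purpose as "a mechanist link between bacteria richness and diversity with disease progression", so it names richness as well as diversity.
- **Trial contrast.** Aims of this Study lists gut microbiota diversity among the outcomes on which the intervention plus TAU is to be compared with TAU alone.
- **Rule for other continuous outcomes.** Secondary Analyses prescribes ANCOVA with the baseline value as covariate.

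**The concern.** Two arms measured at two visits give four sets of diversity values. A t-test compares two sets, and the text does not say which two, whether the same patients appear in both, or whether the observation is a patient or a sequence read. The randomised arm is not mentioned in the microbiota paragraph.

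The possible readings differ widely. Some are valid, one rejects far too often and one far too rarely. With the choice left open, it could be made after the data are seen. The one valid reading that follows the sampling scheme most directly, a paired comparison over time, leaves the trial's stated contrast unanswered. What is at stake is the credibility of a named secondary outcome; the primary outcome (DASS-21) is not affected.

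A smaller mismatch sits beside this: richness is named as a target but never derived.

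**Working it through.** The article gives no sample size, power or alpha for the microbiota analysis, so there is no planned figure to reproduce. The check takes each reading of the t-test in turn.

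**Inputs**
- Patients: the Abstract reports 61 with a baseline assessment, so about 30 per arm.
- Alpha: 0.05, as in Sample Size (two-sided assumed).
- Correlation *r* of H' between T0 and T3 in the same patient: not in the documents. Assumed, and shown over a range.
- Equal variance of H' at both visits and normal data: assumed.

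**1. Unpaired test of T0 against T3, patient-level H'**

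The unpaired test uses variance 2σ²/n for the mean difference; the true variance is 2σ²(1 − r)/n. The standard error is therefore too large by a factor 1/√(1 − r), and the real alpha is 2[1 − Φ(1.96/√(1 − r))].

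| r | SE ratio | real alpha (formula) | simulated, 30 patients |
|---|---|---|---|
| 0.3 | 1.20 | 0.019 | 0.021 |
| 0.5 | 1.41 | 0.006 | 0.006 |
| 0.7 | 1.83 | 0.0003 | 0.001 |

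The simulation used 40,000 runs. The price is power: for a shift of 0.5 SD at r = 0.5 with 30 patients, power is 0.48 unpaired against 0.76 paired.

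**2. Test on pooled reads**

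If reads are pooled within a group and the variance of H' is taken from read counts, variation between patients is left out. In an illustrative simulation (two groups of 30 patients with no true difference, 100 taxa, Dirichlet-multinomial counts, 1,000 runs) the rejection rate at nominal 0.05 was 0.66 at 1,000 reads per sample and 0.87 at 10,000. The taxa, read depths and between-patient spread are assumptions. The direction and the growth with depth matter more than the exact values.

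**3. Paired test of T0 against T3, patient-level H'**

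Simulated type I error was 0.048 to 0.051 at every assumed correlation from 0 to 0.9, with 30 or 61 patients. The test is valid, but it measures change over time and does not compare the arms.

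**4. Between-arm t-test, patient-level H'**

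With 30 per arm, type I error was 0.048 to 0.049 at T3 and 0.048 to 0.051 on the change from T0. Both are valid and address the stated contrast.

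**5. Precision of the valid between-arm analyses**

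The variance of the arm difference, relative to a T3-only comparison, is 1 for T3 only, 2(1 − r) for change, and 1 − r² for ANCOVA.

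| r | T3 only | change | ANCOVA |
|---|---|---|---|
| 0.3 | 1 | 1.40 | 0.91 |
| 0.5 | 1 | 1.00 | 0.75 |
| 0.7 | 1 | 0.60 | 0.51 |

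Because 1 − r² ≤ 1, and 1 − r² = (1 − r)(1 + r) ≤ 2(1 − r), ANCOVA is never less precise than either t-test, apart from the one degree of freedom spent on the covariate. At r = 0.5 either t-test needs 1/0.75 = 1.33 times as many patients for the same precision.

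**6. Richness**

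The outcomes section names richness and diversity; the analysis section derives only H'. Aims of this Study names diversity alone. The mismatch is therefore with the outcomes section only.

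**The case against.** The strongest reply is that an under-described test is not a wrong test. The analysis paragraph opens by treating the blood and stool biomarkers within individuals between T0 and T3, and then says microbiota was also analysed at those times, which points to pairing. Aims of this Study points to an arm comparison. Both readings, at patient level, keep 5%. In addition, a condensed article may leave pairing and unit to a fuller document that is not shown.

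Much of this stands. A reader might infer that the p-values are wrong whichever test is meant. The documents do not support that: nothing says that the test is unpaired or that its variance comes from reads.

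A reader might also infer that GelComparII is unsuitable for sequencing data, or that the clustering undermines the inference. The article gives only the product name, so the first would rest on outside knowledge. UPGMA is a descriptive step to which no p-value is attached, so it cannot distort one.

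Nor is it right to say that sequencing depth is ignored. Equimolar pooling evens out the input, although it does not guarantee equal read counts.

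The appeal to condensation goes less far. The article does not defer the test; it names one. The test it names differs from the baseline-adjusted ANCOVA that it spells out for other continuous outcomes, and the paragraph naming it does not mention the arm.

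**Conclusion.** The point holds as a badly fixed analysis, not as a proven error. As written, the test of microbiota diversity can be run in ways that range from a strongly inflated false-positive rate (pooled reads) to a strongly deflated one (unpaired over time; about 0.02 to 0.0003 for r from 0.3 to 0.7). Of the readings that keep 5%, the paired one does not answer the stated comparison with TAU. The between-arm ones do answer it, but are at best as precise as ANCOVA and usually less so: relative variance 1 for either t-test against 0.75 at r = 0.5.

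The precision ranking follows from algebra under equal variances and a linear relation between T0 and T3. Its size depends on a correlation that the documents do not give. The read-level figures depend on an assumed abundance model. The richness mismatch is minor. No primary conclusion is touched.

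**What to change.** In Data Analysis, Biomarkers:

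1. State that one Shannon H' is derived per patient per visit and that the patient is the unit of analysis.
2. Replace the t-test with ANCOVA of T3 H' on randomised arm, with T0 H' as covariate. This brings the outcome into line with Secondary Analyses.
3. Label the UPGMA clustering as descriptive only.
4. Either derive a richness index per patient per visit at a common read depth and analyse it in the same way, or delete richness from the Biomarkers text under Primary and Secondary Outcomes in the RCT.

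Rarefying all samples and adding a permutation test of composition such as PERMANOVA are options; this point does not require them.

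The cost is wording and a standard model on samples already collected. ANCOVA needs a T0 and a T3 sample from each patient, so a patient lacking one is lost unless the multiple imputation described under Attrition, Protocol Non-adherence, and Missing Data is applied here too. If richness is kept, samples below the chosen read depth drop out of that analysis.

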## Discussion

Among those designed for or tested in IBD, the LIFEwithIBD intervention is the first to integrate ACT and compassion approaches. The RCT presented in this protocol paper will provide evidence on the efficacy of this intervention (which was delivered along with TAU) in improving health outcomes in comparison to the exclusive delivery of TAU (medical treatment). Due to the inactive nature of the control condition, future studies should compare the intervention's efficacy to other conditions such as active controls (e.g., psychoeducation) and other psychological interventions tested in IBD, such as Cognitive and Behavioral Therapy (86) or Hypnotherapy (87). The use of an inactive control will indeed be a significant limitation to this RCT, especially considering that participants allocated to this condition were aware of their non-allocation to the intervention group, which may influence answers to the administered self-report questionnaires. Also, contact with a group of people with the same pathology, as well as with the therapists, may in itself provide therapeutic effects only experienced by the experimental group, which adds to the disparity between the study groups. Nevertheless, considering this is the first time the LIFEwithIBD intervention will be tested, the use of an inactive control may provide useful preliminary results on the effects of the intervention.

The greatest limitation to this RCT appears to be participant retention, similarly to previous RCTs testing group interventions in this population, which also showed large attrition rates (25, 86). In the current study this may have been due to participants not being compensated for their participation besides receiving the intervention. Results from this RCT will act as support for future studies testing the LIFEwithIBD intervention or other acceptance and/or compassion-based interventions for IBD.

## Ethics Statement

This study was reviewed and approved by Coimbra Hospital and Universitary Center (CHUC), Coimbra, Portugal. Patients/participants provided their written informed consent.
